#### Sample size

The sample is calculated based on the assumption that the 5-year local recurrence rate in the control arm is 5% with an exponential distribution. We hypothesize that the use of 1-week course of adjuvant radiotherapy will not increase the locoregional recurrence beyond 8% (absolute difference of 3%), corresponding to a hazard ratio of 1.63. We further assume that patients will be accrued over 5 years with an initial ramp-up in the first year and that 2% of the patients will be lost to follow-up each year of the trial. The total trial duration is expected to be 10 years to ensure a minimum follow-up of 5 years for the last patient. For a fixed sample size design to achieve the required number of events to achieve a one-sided type I error of 0.025 and a power of 80% the total number of events required is 140. The total planned sample size is 2100 patients.

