## Assignment of interventions: allocation

### Sequence generation {16a}

Stratified randomization using permuted blocks will be used for randomization. The randomization sequence will be generated using the Robust Randomization App (available at https://clinicalresearch-apps.shinyapps.io/rrapp/) or a similar application and the randomization scheme generated from the app will be then used with the RedCap Randomization module to generate the randomization sequence. Patients will be allocated into the two groups in a 1:1 ratio. The following stratification factors will be used:
Type of surgery: mastectomy or breast conservationRegional nodal radiation: required or notTriple-negative breast cancer: yes or noInstitute

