### Interim analyses {21b}

An interim analysis will be planned once 50 patients are accrued in each arm, and in this analysis, we will be evaluating the acute toxicity of the two interventions. The sample size of 50 patients in each arm allows us 80% power to exclude a within-group rate of CTCAE Grade 3 or more acute skin toxicity exceeding 10% (absolute increase) over the target rate of 5% (one-sided type I error of 5%).

The next interim analysis for safety (in terms of locoregional recurrences) will be planned at 3 years when 16 events in total are expected to have occurred. As a result of this interim analysis, the sample size has been increased to 2100 patients (from 2074 without the interim analysis). The critical *Z* value at the time of interim analysis is 3.47 for futility. The following table illustrates the key features of the design (Table 4).

**Table 4 Tab4:** Tabulation of the features of the interim analysis for loco-regional recurrence

Analysis	Value	Efficacy	Futility
**IA1: 11%**	*Z*	3.47	− 1.48
*N*: 1184	*p* (1-sided)	0.0003	0.9318
Events: 16	HR at bound	0.28	3.47
Year: 3	*P* (cross) if HR = 1.63	0.0003	0.07
	*P* (cross) if HR = 1	0.0056	0.008
**Final**	*Z*	1.96	1.96
*N*: 2100	*p* (1-sided)	0.025	0.025
Events: 140	HR at bound	1.17	1.17
Year: 10	*P* (cross) if HR = 1.63	0.025	0.975
	*P* (cross) if HR = 1	0.800	0.200

Asymmetric two-sided group sequential design with binding futility bound, 2 analyses, time-to-event outcome with sample size 2100 and 140 events required, 80% power, 2.5% (1-sided) type I error to detect a hazard ratio of 1 with a null hypothesis hazard ratio of 1.63. Enrollment and total study durations are assumed to be 5 and 10 years, respectively. Efficacy bounds derived using a Lan-DeMets O’Brien-Fleming approximation spending function. Futility bounds derived using a Lan-DeMets O’Brien-Fleming approximation spending function. 1A1 11% = 1st interim analysis done when 11% of the local recurrence events have been observed (information fraction)

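### Table 4's interim bounds cannot come from the Lan-DeMets O'Brien-Fleming spending its footnote names; recomputing with that function would nearly remove the harm stop

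*Protocol article*

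**What the plan says.** Section Interim analyses {21b} plans a look at locoregional recurrence at 3 years, when 16 events are expected. Table 4 puts this at 11% information. Its footnote describes a two-analysis design with a binding futility bound and gives the source of each boundary: "Efficacy bounds derived using a Lan-DeMets O’Brien-Fleming approximation spending function" and "Futility bounds derived using a Lan-DeMets O’Brien-Fleming approximation spending function". The design parameters are "80% power, 2.5% (1-sided) type I error to detect a hazard ratio of 1 with a null hypothesis hazard ratio of 1.63", with "time-to-event outcome with sample size 2100 and 140 events required".

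For the interim, Table 4 prints:
- Efficacy: Z 3.47, one-sided p 0.0003, hazard ratio at the bound 0.28, crossing probability 0.0056 at HR 1.
- Futility: Z -1.48, hazard ratio at the bound 3.47, crossing probability 0.07 at HR 1.63 and 0.008 at HR 1.

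The final Z is 1.96. The running text attributes a sample-size increase to this look: "the sample size has been increased to 2100 patients (from 2074 without the interim analysis").

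**The concern.** O'Brien-Fleming-type spending is extremely sparing early on. At 11% information it should release almost none of the type I or type II error, yet the table releases 0.0003 of alpha and 0.008 of beta and charges 26 extra patients for the look. Label and numbers appear to belong to different designs.

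This matters because a spending function is the rule for resetting bounds when the observed event count differs from the planned one. The look is tied to 3 years, and 16 is what is expected by then, so the actual count will probably differ. Whoever applies the footnote at that point gets boundaries quite unlike those in the table. The futility bound is the one that would stop the trial for excess recurrence on the 1-week schedule.

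**Working it through.** **Inputs.** One-sided alpha 0.025, power 80% (beta 0.20), null HR 1.63, alternative HR 1, 140 final events (Sample size; Table 4 footnote); 1:1 allocation (Sequence generation {16a}); 16 interim events, so t = 0.11 as printed or 16/140 = 0.114; binding futility. The margin checks: ln 0.92 / ln 0.95 = 1.626.

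**1. Internal consistency of the printed row.** With 1:1 allocation, the hazard ratio at a bound Z with d events is 1.63 × exp(-2Z/√d). At d = 16, Z = 3.47 gives 0.29 (printed 0.28) and Z = -1.48 gives 3.42 (printed 3.47). The upper-tail probability of 3.47 is 0.00026 (printed 0.0003), and Φ(-1.48) = 0.069 (printed 0.07). The row agrees with itself up to rounding of t, so this is not a typing slip in one cell.

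**2. Spending under the named function.** Lan-DeMets O'Brien-Fleming: a(t) = 2[1 - Φ(z(1-a/2)/√t)].
- Alpha 0.025, z = 2.2414: 1.4e-11 at t = 0.11 and 3.4e-11 at t = 16/140, giving efficacy Z 6.66 and 6.53.
- Beta 0.20: 0.00011 and 0.00015.

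**3. Two-look solution with binding futility.** Let θ be the mean of the final Z under HR 1. The futility bound is l = θ√t + Φ⁻¹(β(t)). The final bound c makes total alpha 0.025, θ is set for exactly 80% power, and inflation is (θ/(1.960 + 0.842))².
- Named function at 16/140: θ = 2.802, so l = 0.947 - 3.615 = -2.67. At t = 0.11, l = -2.76.
- Taking θ from 140 events and ln 1.63 instead gives l = -2.64 at 16/140.

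**4. Search for a function that fits.** Hwang-Shih-DeCani: a(t) = a(1 - e^(-γt))/(1 - e^(-γ)). At t = 0.11, γ = -4 spends 0.025 × 0.5527/53.60 = 0.000258 of alpha, and γ = -2 spends 0.20 × 0.2461/6.389 = 0.0077 of beta.

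| Interim quantity | Table 4 | Named function, t = 0.11 to 0.114 | Hwang-Shih-DeCani -4/-2, t = 0.11 |
|---|---|---|---|
| Efficacy Z | 3.47 | 6.66 to 6.53 | 3.47 |
| P(efficacy, HR 1) | 0.0056 | about 1e-8 | 0.0056 |
| Futility Z | -1.48 | -2.76 to -2.64 | -1.49 |
| P(futility, HR 1.63) | 0.07 | 0.003 to 0.004 | 0.068 |
| P(futility, HR 1) | 0.008 | 0.0001 to 0.00015 | 0.0077 |
| Final Z | 1.96 | 1.96 | 1.96 |
| 2074 inflated to | 2100 | 2074 | about 2092 |

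Solving for gamma from the printed values at 16/140 gives -4.05 and -2.01.

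**5. Can another reading rescue the footnote?** The named function needs t = 0.38 for Z = 3.47 but t = 0.23 to spend 0.008 of beta, so no single information fraction works. Classical O'Brien-Fleming gives Z of about 5.8, the named function with alpha 0.05 gives 5.68, and Pocock-type spending gives about 2.6. None fits.

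**6. Consequence at 16 events.** The chance of crossing the futility bound l is Φ(l - 2[ln 1.63 - ln HR]).

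| True HR | Printed bound (-1.48) | Named function (-2.64) |
|---|---|---|
| 1.63 | 7% | 0.4% |
| 2.5 | 27% | 4% |
| 3 | 40% | 8% |
| 4 | 62% | 20% |

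The hazard ratio needed to cross is 1.63 × exp(2.64/2) = 6.1 under the named function, against 3.4 to 3.5 as printed. At other counts, the named function and the matching one give about 8.1 versus 3.8 at 14 events, and 4.2 versus 2.8 at 20.

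**The case against.** The strongest reply is that this is a labelling error with little effect. The final critical value is 1.96 under either function, and overall alpha, power, the 140 events and the non-inferiority test are untouched. Table 4 prints every bound, so a user who applies it at 16 events is not misled; in that case only the label is false. The article gives no explicit rule for recomputing, and the SAP, not shown, may name the operational function. An independent monitoring committee with a statistician could act on safety without crossing a bound. Hwang-Shih-DeCani is not named anywhere, and it takes 2074 only to about 2092, not 2100.

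Much of this stands. The damage is confined to the interim look, it depends on someone recomputing with the named function, and the identity of the true function is an inference. The 8-patient gap is unexplained; rounding of events or enrolment might account for it, but that is not shown. None of this reconciles the footnote with the table. With 16 only an expected count, recomputation is the ordinary use of a spending function, and a committee that turns to the article for the rule is given the wrong one. The running text adds to the confusion by calling 3.47 the futility Z, where Table 4 lists it as the efficacy Z.

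**Conclusion.** The concern holds. The named function does not produce the interim bounds or the 26-patient increase, and the gap (efficacy Z 6.5 to 6.7 against 3.47; futility Z -2.6 to -2.8 against -1.48) is far beyond rounding. It persists at t = 0.11 and 0.114 and under both ways of setting the drift. Hwang-Shih-DeCani with gamma -4 and -2 is the probable source of the bounds. If the footnote were followed at the interim, the probability of a harm stop would fall from 7% to about 0.4% at the margin itself and from 27% to about 4% at a true hazard ratio of 2.5. These figures assume a look at 16 events, 1:1 allocation and the usual normal approximation for the log hazard ratio. The final analysis is not affected. The correction is needed because the documented rule for a stopping threshold is wrong as written.

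**What to change.** Retrieve the design-software output and establish which spending functions and parameters were used. Then make the footnote, the interim rows of Table 4 and the stated inflation agree:
- If the printed bounds are kept, replace both footnote sentences with the functions actually used (Hwang-Shih-DeCani with gamma -4 for efficacy and -2 for futility reproduces the bounds). State that these govern recomputation at the observed event count, and explain how 2074 became 2100.
- If O'Brien-Fleming spending was really intended, replace the interim rows and withdraw the 26-patient inflation.

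In the same edit, correct the running text on which bound 3.47 refers to. The first route costs a footnote and matching SAP wording and leaves the trial unchanged; the second changes the interim boundaries. Either must be settled, and given to the monitoring committee, before the interim data are seen.

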### Methods for additional analyses (e.g. subgroup analyses) {20b}

The following pre-specified subgroup analyses will be conducted on the primary and the other time to event endpoints stratified by:
Menopausal status: premenopausal vs postmenopausalNodes positive: none vs 1–3 vs > 3Subtype: luminal vs Her2-enriched vs TNBCRegional nodal radiation: none vs SCF alone vs IMN + SCFBoost type: SIB vs sequential boost

These subgroups are chosen as they have an implication on the primary as well as the secondary time to event outcomes and are independently prognostic. Results will be presented as forest plots with interactions results alongside. The interaction test will test if the treatment effect is modified by the subgroup.

In order to evaluate the impact of prognostic factors on the treatment effect, a nomogram will be built using Cox regression that includes treatment as a factor. The use of this nomogram will enable the user to judge the benefit arising from the use of a particular fractionation regimen in a patient with a given combination of prognostic factors.

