### Intervention description {11a}

#### Overview

Patients will be randomized into two arms equally:
Control Arm: 40 Gy in 15 fractions over 3 weeks to the whole breast or chest wall. Patients undergoing breast conservation therapy will receive additional boost radiotherapy to the tumour bed. The supraclavicular fossa will be treated in patients with node-positive disease or those receiving neoadjuvant chemotherapy. IMC and axillary radiotherapy will be given as per the institutional policy. Boost radiotherapy will be delivered using SIB of 8 Gy in 15 fractions (or alternatively using a sequential boost of 12 Gy in 4 fractions)Test Arm: 26 Gy in 5 fractions over 1 week to the whole breast or chest wall. Treatment volumes will be the same as the control arm. Additional boost will be delivered to patients who have undergone breast conservation. Boost radiotherapy will be delivered using SIB of 6 Gy in 5 fractions (or alternatively using a sequential boost of 12 Gy in 4 fractions)

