#### Radiotherapy

Radiotherapy should be started within 12 weeks of the last date of surgery or last cycle of planned adjuvant chemotherapy. All patients would be treated on linear accelerators (6–15 MV energies). Radiotherapy planning would be performed on volumetric planning CT scans with a pre-defined simulation protocol. Patients with left-sided breast cancers should preferably receive cardiac sparing radiotherapy. Field-based planning for the breast and chest wall is allowed in the protocol where anatomical landmarks are identified and coverage ensured. This is the current practice in most of the centres in this trial.

The organs at risk to be delineated include the ipsilateral and contralateral lung, heart and the contralateral breast. In patients undergoing radiotherapy for left-sided breast, the left anterior descending artery may also be delineated [24]. The brachial plexus may be delineated in patients undergoing regional nodal radiation [25].

Tangential beams would be utilized for irradiating the breast or chest wall, while regional nodal radiation should be delivered using a technique that ensures no overlap of the field—in most patients, this would imply an enface field to cover the supraclavicular fossa (SCF) with a half beam block or a collimator-couch rotation-based technique. Dose will be prescribed at a point in the midplane for the breast and chest wall for tangents. For patients receiving SCF radiation, the dose will be prescribed at the depth of maximum dose (Dmax). In patients who have undergone breast conservation, boost will be delivered using the technique used in the institute. The use of a volumetric modulated arc therapy (VMAT)-based simultaneous integrated boost (SIB) for tumour bed irradiation is allowed. Inverse planned radiation is allowed for patients receiving radiation to the internal mammary nodal chain.

Dose in the target volume should be homogenous and use of a forward planned field in field IMRT technique is allowed. Alternatively, centres can specify the technique to be used for ensuring dose homogeneity. Individualized treatment planning will be done with a target to ensure that the breast/chest wall is covered with 95% of the prescribed dose and that the maximum dose does not exceed 107% of the prescribed dose. In patients undergoing VMAT simultaneous tumour bed boost (SIB), the dose to the boost target volume will be restricted to < 107% of the total dose (Table 2).

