## Assignment of interventions: blinding

### Who will be blinded {17a}

Given the nature of intervention used in the study, no blinding is planned in this study.

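### Two subgroup interaction tests (SIB vs sequential boost; SCF alone vs IMN + SCF) use treatment features that need not be declared before the open-label allocation, so selection can bias them

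*Protocol article*

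**What the plan says.** **Subgroups.** The section Methods for additional analyses {20b} lists five subgroups for the primary and other time-to-event endpoints. Two are extent of regional nodal radiation (none, SCF alone, IMN + SCF) and boost type (SIB, sequential). The text runs them together: "none vs SCF alone vs IMN + SCFBoost type". The stated reason is: "These subgroups are chosen as they have an implication on the primary as well as the secondary time to event outcomes and are independently prognostic". Forest plots are planned, and "The interaction test will test if the treatment effect is modified by the subgroup".

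**Boost.** Under Intervention description {11a}, Overview, both techniques are open in each arm. Control: "Boost radiotherapy will be delivered using SIB of 8 Gy in 15 fractions (or alternatively using a sequential boost of 12 Gy in 4 fractions"). Test: "Boost radiotherapy will be delivered using SIB of 6 Gy in 5 fractions (or alternatively using a sequential boost of 12 Gy in 4 fractions"). No rule for choosing is given. The Radiotherapy section adds that after breast conservation "boost will be delivered using the technique used in the institute", and that a VMAT-based SIB is permitted.

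**Internal mammary nodes.** "IMC and axillary radiotherapy will be given as per the institutional policy". The Overview also says that the test arm has the same volumes as the control arm.

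**Before allocation.** Sequence generation {16a} stratifies by type of surgery, nodal radiation required or not, triple-negative status and institute. Implementation {16c} has these entered before the randomise button is clicked. Neither boost technique nor internal mammary intent is named there.

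**Blinding.** "Given the nature of intervention used in the study, no blinding is planned in this study"

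**The concern.** A subgroup comparison keeps the protection of randomisation only if membership cannot respond to the allocation. Boost technique and internal mammary coverage belong to the radiotherapy plan, and in an open-label trial nothing in the article stops them from being settled once the arm is known. If clinicians choose differently by arm, and the choice is also related to recurrence risk, then the two arms within SIB, or within IMN + SCF, contain different kinds of patients. The subgroup hazard ratios then mix selection with treatment effect, and the interaction test can show modification that is not there or hide modification that is.

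This matters because the Discussion lists SIB to the tumour bed and internal mammary nodes in five fractions among the trial's novel elements. Readers will look to these two subgroups for evidence on that element.

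**Working it through.** **1. Is arm-dependent choice possible on the article's own text?**
- The rationale section says that a genuine one-week course needs the boost to be given as SIB. That reason applies only to the test arm.
- The note to the participant timeline (Table 3) puts the post-treatment assessment after a sequential boost in week 2 (test) or week 4 (control). The added week roughly doubles the test course (1 to 2 weeks) but lengthens the control course by a third (3 to 4 weeks).
- The SIB dose differs by arm (8 Gy, 6 Gy), while the sequential boost is the same in both (12 Gy in 4). Boost type is therefore partly a feature of the allocated treatment.

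These points show that arm-dependent choice is possible, not that it happens.

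**2. The plan's own figures, used below only for scale.**
- Margin: ln(0.92)/ln(0.95) = 1.626, stated as 1.63.
- Events at one-sided 0.025 and 80% power, Freedman formula: 139 at HR 1.626, against the stated 140.
- HR at the final bound: 1.63 × exp(−1.96 × 2/√140) = 1.17, as in Table 4.

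The article gives no figure for the subgroup tests.

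**3. Size of the bias with no true effect.** The article gives no selection rates, so these are assumptions. A quarter of patients have 10% five-year risk and three quarters have 3.33%, so the mean is 0.25 × 10 + 0.75 × 3.33 = 5.0%, the planned control rate. Option A is either level of the subgroup variable and B is the other. The rate in A within an arm is

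(0.25 × pH × 10% + 0.75 × pL × 3.33%) / (0.25 × pH + 0.75 × pL),

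where pH and pL are the proportions of high-risk and low-risk patients given A. For B, use 1 − pH and 1 − pL. The subgroup HR is ln(1 − test rate)/ln(1 − control rate).

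| Scenario | Test pH / pL | Control pH / pL | A: test vs control | B: test vs control | HR in A | HR in B | Ratio |
|---|---|---|---|---|---|---|---|
| Same rule, risk-driven | 30% / 60% | 30% / 60% | 4.3% vs 4.3% | 5.8% vs 5.8% | 1.00 | 1.00 | 1.00 |
| Mild | 60% / 60% | 50% / 60% | 5.0% vs 4.8% | 5.0% vs 5.3% | 1.05 | 0.94 | 1.11 |
| Moderate | 70% / 70% | 40% / 60% | 5.0% vs 4.5% | 5.0% vs 5.6% | 1.10 | 0.90 | 1.23 |
| Strong | 85% / 75% | 30% / 60% | 5.2% vs 4.3% | 4.4% vs 5.8% | 1.21 | 0.76 | 1.59 |

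Example, strong, option A: the test rate is (0.25 × 0.85 × 10 + 0.75 × 0.75 × 3.33)/(0.2125 + 0.5625) = 4.0/0.775 = 5.2%. The control rate is (0.75 + 1.5)/0.525 = 4.3%.

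**4. How often would the interaction test reject?** Poisson simulation with 20,000 runs, true HR 1, events scaled to 140 in 2100 patients, two-sided 5%. The share of patients in the subgroup analysis is assumed.

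| Scenario | 30% of patients | 50% | 100% |
|---|---|---|---|
| Same rule | 4% | 5% | 5% |
| Mild | 4% | 5% | 6% |
| Moderate | 5% | 6% | 8% |
| Strong | 5% | 10% | 19% |

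Events are few. If 70 events fall evenly in four cells, the standard error of the log ratio is √(4/17.5) = 0.48, about as large as ln(1.59) = 0.46. A misleading forest plot is therefore more likely than a significant false interaction.

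**The case against.** The strongest case against is that institute, not the individual clinician, determines both variables. Boost follows institute technique, internal mammary treatment follows institutional policy, volumes are to be the same in both arms, and institute is a stratification factor. The Discussion even says that the study will use a VMAT-based SIB approach. A fixed rule applied equally to both arms gives no bias, as the first row of the table in step 3 shows. This stands as a real limit on the risk. It does not remove it: the Overview leaves two boost options open within each arm, no text holds a centre to one of them in both arms, and a SIB versus sequential subgroup presupposes that both will be used.

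Three stronger readings are tempting, and the article does not support them.
- *That these variables are known to be recorded after allocation.* This would rest on the title of a radiotherapy plan form under Plans for assessment and collection of outcomes. The form contents are not shown, and the same list has a screening form and a pretreatment form. What can be said is that declaration before allocation is not required in the article.
- *That the whole nodal subgroup is exposed.* No nodal radiation versus any is a stratification factor. Only SCF alone versus IMN + SCF is open.
- *That selection would produce an interaction as large as the non-inferiority margin.* Only strong assumed selection gives a ratio near 1.6, and 1.63 limits a between-arm hazard ratio, not a ratio of subgroup hazard ratios.

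It may also be said that defining subgroups by intent or by delivery belongs in the analysis plan, which is not shown. The detail may well be there. But the article itself fixes the variables and the interaction tests, and the remedy acts on what is entered at randomisation.

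**Conclusion.** The point holds in limited form. Interaction by boost type, and by SCF alone versus IMN + SCF, is to be tested on features of the delivered treatment that the article does not require to be declared before an open-label allocation. Bias arises only if the choice depends on both arm and prognosis. The article neither shows that this happens nor prevents it. Under the assumed risk mix, the spurious ratio of hazard ratios is 1.11 for mild selection, 1.23 for moderate and 1.59 for strong, and 1.00 for a common choice rule. False-positive interaction rates stay near 5% except under strong selection: about 10% if half the patients are in the analysis, 19% if all are.

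The primary comparison of the randomised arms is unaffected, as are the other three subgroups and the split between no nodal radiation and any. This is a worthwhile, inexpensive improvement to two secondary analyses, not a threat to the trial's main conclusion.

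**What to change.** - Add two required REDCap fields, completed before the randomise button can be used: intended boost technique (none, SIB, sequential) and intended internal mammary coverage.
- Define the boost-type subgroup and the SCF alone versus IMN + SCF subgroup by these intended values, and run the interaction tests on them.
- Report delivered technique by arm as a descriptive table, without an interaction test.
- For patients already randomised without a recorded intent, use the institute's documented policy at the time of randomisation. Where none exists, use only the stratification factor (nodal radiation required or not).

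Cost: two extra fields and a change of wording. Sample size, event target and treatment do not change. Intended and delivered technique will differ for some patients, and early patients will lack a recorded intent. At the article's status date of 7 June 2020, 420 of 2100 patients (20%) had been randomised, so intent could then still have been recorded prospectively for the remaining 1680 (80%).
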